#### Sample size

The sample size is based on the main outcome: depressive symptoms in pre-vocational students in first and second year classes. Based on a meta-analysis by Stice et al. [24], we assume an effect size of *d* = 0.20. Thus, we want to test the hypothesis that we will find an effect of *d *= 0.20 (or larger) at 6 months follow-up. This will be tested at a two-sided significance level of 5% and a power of 80%. Accounting for the clustering in the data with 22 students on average per class, an intraclass correlation of 0.02, a cluster size variation of 0.17 and a baseline correlation of 0.30, we need *n* = 315 students in each condition. Furthermore, we expect that approximately 40% of parents and/or students will not provide informed consent. In order to secure the needed sample size, the aim is to sample 525 students per trial. Assuming an average of 4 classes of 22 students per school (divided across intervention and control condition), this will require 48 classes from about 12 schools.

The sample size calculation was performed in Stata version 14.2 statistical software package using the clustersampsi-procedure. The intraclass correlation coefficient (ICC) of 0.02 was based on two studies: the Dutch Health Behaviour in School-aged Children Survey (HBSC) [32], where the ICC on the emotional scale within the Strengths and Difficulties Questionnaire (SDQ) was 0.008 (95% CI: 0.003-0.02) and a large European study where the ICC’s for depressive mood varied across countries from 0.01 to 0.07 [33].

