**Methods:**

A cluster randomized controlled trial (RCT) with students randomized to HL or to care as usual will be conducted. Pre-vocational students in their first or second year (aged 12 to 14) will participate in the study. Subjects in both conditions will complete assessments at baseline and at 3- and 6-months follow-up. The primary outcome will be depressive symptoms using the Center for Epidemiologic Studies Depression Scale (CES-D) at 6-months follow-up. Secondary outcomes are well-being using the Warwick-Edinburgh Mental Well-Being Scale (WEMWBS) and life satisfaction (Cantril Ladder) measured at 6-months follow-up. Alongside the trial, an implementation study will be conducted to evaluate the implementation of HL, using both quantitative and qualitative methods (interviews, survey, and classroom observations).

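### For the 6-month comparison, 315 students per condition does not follow from the listed inputs; under those inputs it gives about 59–65% power, not 80%

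*Protocol article*

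**What the plan says.** The Sample size section sets out a full calculation. The effect is fixed ("we assume an effect size of *d* = 0.20"), and the hypothesis concerns that effect "or larger) at 6 months follow-up". It is to be "tested at a two-sided significance level of 5% and a power of 80" per cent. Clustering enters "with 22 students on average per class", followed by "an intraclass correlation of 0.02, a cluster size variation of 0.17 and a baseline correlation of 0.30, we need" 315 students in each condition.

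The section then allows for non-consent: "we expect that approximately 40% of parents and/or students will not provide informed consent". This leads to 525 students to approach and to 48 classes from about 12 schools. The software procedure is named (clustersampsi in Stata). The section mentions neither averaging over follow-ups nor a correlation between the two follow-up scores.

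The abstract and the Aim section also place the primary depression outcome at 6 months. The Statistical analyses section plans a linear mixed model with time, condition and their interaction, adjusted for the baseline score, and reports between-group effects at each time point.

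**The concern.** The inputs and the result are both printed, so they can be checked against each other, and they disagree. A standardised effect of 0.20 with a two-sided 5% test and 80% power needs more than 390 per arm under individual randomisation. A baseline correlation of 0.30 removes only 9% of that, and clustering adds to it. A requirement of 315 is below what an unclustered trial would need.

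The figure sets the recruitment target and supports the power claim for the only primary hypothesis. If the listed inputs are right, the trial would miss a true d of 0.20 about 35–40% of the time, not 20%, and a null result would be read as stronger evidence against that effect than it is.

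**Working it through.** **Inputs** (protocol article, Sample size): d = 0.20 with SD 1; z-values 1.960 and 0.842; m = 22; ICC = 0.02; cluster size variation 0.17, read as a coefficient of variation (CV); baseline correlation r = 0.30; consent 60%. Allocation of classes is equal (Design of the RCT).

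**What follows from 315.** 315/0.60 = 525, so 525 is a per-condition number. 48 × 22 = 1,056 students approached, and 1,056 × 0.60/2 = 317 consenting per condition. These steps agree with 315. The question is where 315 comes from.

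**Requirement for one 6-month comparison**

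1. Individual randomisation: 2(1.960 + 0.842)²/0.20² = 392.4, so 393 per arm.
2. Baseline adjustment: 1 − 0.30² = 0.91; 392.4 × 0.91 = 357.1, so 358 per arm. This already exceeds 315 with no clustering.
3. Design effect for unequal clusters, 1 + [(1 + CV²)m − 1] × ICC: with m = 22, 1 + (1.0289 × 22 − 1) × 0.02 = 1.433.
4. 357.1 × 1.433 = about 512 per condition. Dropping the CV term changes little: the design effect becomes 1.42 and the need about 507.
5. With 0.60 × 22 = 13.2 consenting students per class, the design effect is 1.252 and 357.1 × 1.252 = about 447.

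**Power with 315 per condition**

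| | m = 22 | m = 13.2 |
|---|---|---|
| SE = √(2 × design effect × 0.91/315) | 0.0910 | 0.0850 |
| Power at d = 0.20, normal approximation | 59.4% | 65.2% |
| Power, t-test with cluster df (about 27; 46) | 56% | 63% |
| d detectable with 80% power | 0.255 | 0.238 |

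Across the ICCs cited in the section (0.008 to 0.07), power at 315 runs from 68–71% down to 38–48%. None of these figures includes loss to follow-up.

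**Attempts to reach 315**

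- Crediting a factor of 1 − r = 0.70 in place of 1 − r² gives 394 (m = 22) or 344 (m = 13.2).
- Keeping 1 − r², the baseline correlation would have to be about 0.66 (m = 22) or 0.60 (m = 13.2).
- ANCOVA on the mean of the 3- and 6-month scores, with correlation 0.30 between all three assessments, has variance factor (1 + 0.30)/2 − 0.30² = 0.56. Then 392.4 × 1.4327 × 0.56 = 314.9, and 315 gives 80.0% power.
- A one-sided test with a factor of 1 − r gives 310, but the stated test is two-sided.

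**The case against.** The strongest reply is that 315 can be reproduced. The averaged-follow-up calculation uses the stated d, significance level, power, class size, ICC and CV, and the trial does have two follow-ups in a repeated-measures model. So a reader who concludes that no calculation based on these inputs yields 315 goes too far. The match is close enough to be a plausible origin.

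It does not support the printed claim, for three reasons. It needs a correlation between the 3- and 6-month scores, which the article does not state. It powers the average effect over 3 and 6 months, whereas the section, the abstract and the aim all name 6 months. And in a mixed model with time-by-condition terms and complete data, the 3-month score adds essentially nothing to the 6-month contrast.

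A second reply is that an input may be misprinted while 315 is correct. That stands. A reader might infer that the trial's true power is 59–65%, but the article does not establish this: the range is conditional on every listed input being the one intended.

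A third reply is that 525 exceeds 512, and 525 analysed students per condition in classes of 22 would give about 81% power. But 525 is the number approached, and the section expects only 60% of them to consent.

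Finally, the 13.2 per class is derived, and it keeps the CV at 0.17 although uneven consent could raise it. The 65% end of the range is therefore the optimistic one.

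**Conclusion.** The point holds as an internal contradiction: for the 6-month hypothesis as written, the listed inputs require about 512 per condition (about 447 with the consenting class size), not 315. The conclusion does not hang on the choice of design-effect formula, because 358 are needed with no clustering at all.

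Taken at face value, the inputs give 315 per condition a power of about 59–65% at d = 0.20 (56–63% with cluster degrees of freedom), and 80% power only at d of about 0.24 to 0.255. This rests on the usual 1 − r² reduction for baseline adjustment, an ICC of 0.02 and no attrition. Whether the number or one of the inputs is at fault, or the calculation was aimed at the average of the two follow-ups, cannot be settled from the article. Nothing elsewhere in it resolves the discrepancy.

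**What to change.** Rerun the calculation for the 6-month comparison and correct the paragraph by whichever of these applies:

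- **If the listed inputs are right**, restate the power at d = 0.20 for 315 per condition (about 56–65%, depending on class size and degrees of freedom) or the effect detectable with 80% power (about 0.24 to 0.255). Preferably use the consenting class size in the design effect. With 48 classes and about 317 consenting students per condition, that means roughly 63–65% power, or 80% power at d of about 0.24.
- **If a different correlation or effect size was entered**, print that value with its source.
- **If the mean of the 3- and 6-month scores was intended**, say so, give the assumed correlation between them, and reconcile this with the 6-month primary outcome.

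Correcting the statement needs no extra enrolment; the cost is a less favourable stated power. Restoring 80% power at d = 0.20 is a separate decision. Under the listed inputs it would take about 447 consenting students per condition at 13.2 per class, which is 447/13.2 = about 34 classes per condition against the present 24, before any allowance for loss to follow-up.

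### The recruitment target of 525 is a per-condition number misstated as the trial total, and the sample size makes no allowance for loss between consent and the 6-month primary assessment

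*Protocol article*

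**What the plan says.** All the figures are in the Sample size section of the protocol article.

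- Effect: "we assume an effect size of *d* = 0.20", for the comparison at 6 months, with two-sided alpha of 5% and 80% power.
- Clustering and baseline adjustment: 22 students per class on average, with "an intraclass correlation of 0.02, a cluster size variation of 0.17 and a baseline correlation of 0.30".
- Result: 315 "students in each condition".
- Inflation: about 40% of parents and/or students are expected not to consent. Then: "In order to secure the needed sample size, the aim is to sample 525 students per trial".
- Classes: with about four classes of 22 per school, divided between the conditions, "this will require 48 classes from about 12 schools".

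Three other sections bear on the point. Under Recruitment of participants and informed consent, parents are asked for consent before the study starts and students sign at the recruitment session. Under Data collection, the baseline questionnaire is completed at the end of that session, while teachers administer the 3- and 6-month questionnaires in class. Under Statistical analyses, linear mixed models are chosen partly because they handle data missing at random.

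**The concern.** Two things do not fit. First, a requirement of 315 in each of two conditions cannot be met by approaching 525 students in the whole trial when 40% are expected to refuse. The same paragraph therefore implies two recruitment totals that differ by a factor of two. Anyone who later compares achieved recruitment with the published plan could take 525 as the trial's target.

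Second, 315 is the number for the 6-month comparison, yet the only inflation covers refusal, which is settled at or before baseline. If the inflation is used up by refusal, 315 is about the number at baseline, and every student without 6-month data takes the trial below its stated requirement. The stated 80% power would then describe the number enrolled, not the number observed at the primary time point.

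**Working it through.** **Inputs (Sample size section).** 315 per condition; non-consent 40%; 22 students per class; 48 classes; ICC 0.02; cluster-size variation 0.17; d = 0.20; two-sided 5%; 80% power. Equal allocation by class is from Design of the RCT. The attrition rate *a* is not given and is assumed below.

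**Step 1: reproduce 525.**
- One condition: 315/(1 − 0.40) = 525, exactly the printed figure.
- Whole trial: 630/(1 − 0.40) = 1,050.
- Classes: 1,050/22 = 47.7, so 48; and 48 × 22 = 1,056.

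The number 525 reproduces only as a per-condition figure. The 48 classes agree with 1,050, not with 525 in total (525/22 = 23.9 classes).

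**Step 2: margin left for loss after consent.**
- Consenting students from 48 classes: 1,056 × 0.60 = 633.6, or 316.8 per condition.
- Largest loss that still leaves 315: 1 − 315/316.8 = 0.0057, about 0.6%.

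The margin is 1.8 students per condition and comes from rounding up to whole classes.

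**Step 3: size under assumed attrition.** The plan's 315 is taken at face value as giving 80% power at d = 0.20. Power is then Φ[(1.960 + 0.842) × √(1 − a) − 1.960], and the effect detectable with 80% power is 0.20/√(1 − a).

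| Assumed loss by 6 months | Left per condition, from 1,056 approached | Left per condition, from 1,050 approached | Power | Detectable d |
|---|---|---|---|---|
| 0% | 317 | 315 | 80% | 0.200 |
| 10% | 285 | 284 | 76% | 0.211 |
| 15% | 269 | 268 | 73% | 0.217 |
| 20% | 253 | 252 | 71% | 0.224 |

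Power and detectable d are computed from 315 × (1 − a). Starting from 316.8 adds less than half a percentage point of power.

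**Step 4: credit for smaller classes.** If students are lost but classes are not, the average class size falls and so does the design effect, DE = 1 + [(1 + 0.17²)m − 1] × 0.02. At m = 22 it is 1.433; at m = 19.8, 18.7 and 17.6 (10%, 15% and 20% loss) it is 1.387, 1.365 and 1.342. Multiplying (1 − a) in Step 3 by 1.433/DE gives power of about 77%, 75% and 74%.

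On the plan's own scale, then, the missing allowance costs about 4 to 9 percentage points of power at 10% to 20% loss, or about 3 to 6 with the class-size credit.

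**The case against.** **The slip corrects itself.** Schools are recruited and classes are randomised, and the next sentence sets the target at 48 classes, which is twice 525. This stands. A reader might infer that the trial has been planned at half its required size: 525 approached, 315 consenting, about 157 per condition, and roughly 51% power on the scale of Step 3 without the class-size credit. The 48-class figure rules that out. What remains is a wrong statement of the recruitment target.

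**A shortfall at 6 months is inferred, not stated.** This also stands. A reader might conclude that fewer than 315 per condition will certainly be available. The article gives no attrition rate, so it supports only the statement that any loss above about 0.6% produces a shortfall. The rates in the table are assumptions.

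**The design limits the damage.** Assessments take place in regular lessons, participants receive an incentive, and the mixed model uses 3-month data from students who miss the 6-month assessment, under missing at random. This softens the loss of power but does not restore 6-month observations, and the article does not rely on it in place of an allowance.

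**Much lower powers could be quoted.** The standard formula with the stated inputs gives about 512 per condition rather than 315, and 315 then has about 59% power with 22 per class (65% with 22 × 0.60 = 13.2 consenting per class). Those figures mostly reflect a different question, whether 315 follows from its inputs, and should not be charged to missing attrition.

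**Could this be left to a fuller document?** Not here. The article prints the whole chain from 315 to 525 to 48 classes and presents it as securing the needed number. Refusal uses up that chain.

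**Conclusion.** The point holds in two parts. The recruitment target is misstated: 525 is per condition and the trial total is 1,050, consistent with the 48 classes. This is a wording error, not a halved trial. In addition, no allowance is made for loss between consent and the 6-month primary assessment, and the 48 classes leave room for only about 0.6%.

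At an assumed 10%, 15% or 20% loss, about 285, 269 or 253 per condition remain and power is about 76%, 73% or 71% instead of 80%. These figures rest on the assumed rates, on accepting the plan's 315 as giving 80% power, and on counting only students with 6-month data. Shrinking classes would raise them somewhat, and use of 3-month data would offset part of the loss. The first part is certain from the printed numbers. The absence of an allowance in the second part is equally clear, but the size of its effect is not.

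**What to change.** Replace the target with 525 students per condition (1,050 in total; 48 classes). Add an explicit attrition assumption with its basis, give the number per condition expected to have 6-month data, and restate power and detectable d at that number.

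Before restating them, settle whether 315 follows from the stated inputs; that is a separate issue, and the new figures depend on it.

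The cost is about two sentences and a somewhat lower stated power. No extra schools are needed for the correction. Keeping 315 per condition at 6 months is a separate choice: 630/(1 − a)/0.60/22 gives 54, 57 or 60 classes at 10%, 15% or 20% loss, against the 48 planned.

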#### Data collection

Data will be collected through an online questionnaire and students’ self-reports. Students will use their personal HL-accounts (created by the HL-trainer) to gain access to the questionnaires. Data for each assessment and in both conditions will be collected during a regular classroom lesson. At the end of the recruitment session, the research assistant will ask all students to fill in the HL-questionnaire as part of the HL-program. For those participating in the study this data will serve as the baseline measurement (T0) for the RCT. For research purposes, the HL-questionnaire is administered before the start of the HL instead of the second lesson. For the second (T1) and third assessment (T2), teachers are approached to collect and administer the questionnaires in their classes. The duration of each questionnaire will be approximately 15 minutes.

Data collected for research purposes will be stored in a database. For each individual student, a unique respondent number will be used. Students’ names and email addresses will be stored in a separate database, which is only accessible for the data manager of the project.

#### Measures

##### Demographic characteristics

*Demographic characteristics* include gender, birth month and -year and immigration background. Immigration background is assessed by asking the students to indicate their own and both of their parents’ country of birth. Students are considered to have an immigration background if they or at least one of the parents was born in another country then the Netherlands. Students’ educational level is collected via the school.

##### Primary outcome

*Depressive symptoms* will be measured with the Dutch version of the Center for Epidemiologic Studies Depression Scale (CES-D) [34, 35]. The CES-D measures the frequency of 20 depressive symptoms over the past week on a four-point Likert scale. Examples of items are: “I enjoyed life” and “I felt that everything I did was an effort”. Answer categories are: (0) “rarely or none of the time (less than once a week)”, (1) “some or a little of the time (1-2 days a week)”, (2) “occasionally or a moderate amount of time (3-4 days a week)”, or (3) “most or all of the time (5-7 days a week)”. The total score may range from 0 to 60, with higher scores indicating higher levels of depression. The Dutch version has been validated among adolescents and has excellent psychometric properties [31, 36]. Based on previous Dutch findings, we will use a CES-D cut-off score of 16 or higher to identify students with subclinical levels [34] and a cut-off score of 22 or higher to identify students with clinical levels of depression [36].

##### Secondary outcomes

*Well-being* will be measured with the Dutch translation of the Warwick-Edinburgh Mental Well-Being Scale (WEMWBS) [37, 38]. The WEMWBS assesses 14 items on a five-point scale. Scores range from 14 to 70, with higher values reflecting greater perceived well-being. Questions concern feelings experienced in the previous two weeks, such as “I felt good about myself” and “I felt optimistic about the future”. Studies from the United Kingdom found that it is appropriate to use the 14-item WEMWBS to measure well-being among adolescents aged 13 to 16 [39]. In two earlier pilot studies of HL involving pre-vocational students aged 13 to 17, the WEMWBS showed high reliability with Cronbach’s Alpha of 0.84 and higher [31]. The WEMWBS can detect meaningful change at both the group and individual level. At the individual level, minimum detectable change has been set at a change of 3 points [40].

*Life satisfaction* will be assessed with the Cantril Ladder [41]. Students rate how satisfied they are with their life on a visual analogous scale ranging from (0) “the worst possible life” to [10] “the best possible life”. The Cantril Ladder is easily understood and has shown good reliability and convergent validity among young people (e.g., [42]).

*Classmate support* will be assessed by three items indicating the extent to which classmates were experienced as supportive, e.g., “Most of the students in my class are kind and helpful” (Response categories ranging from (1) “completely agree” to (5) “completely disagree”). This is a cross-nationally valid and reliable scale for young people [43].

*Teacher support* will be assessed by three items indicating the extent to which teachers were experienced as supportive, e.g., “I feel that teachers accept me as I am” (Response categories ranging from (1) “completely agree” to (5) “completely disagree”). Cross-national studies showed the scale to be valid and reliable for young people (e.g., [42]).

*Bullying involvement*. Students are asked how many times they were involved in bullying at school in the past four weeks. The response categories available are: (1) “zero times”, (2) “ones or twice”, (3) “about once a week”, (4) “several times a week”. This is a validated measure on bullying involvement that shows good psychometric properties [44].

*Bullying victimization.* Students are asked how many times they have been bullied at school in the past four weeks. Response categories include: (1) “zero times”, (2) “ones or twice”, (3) “about once a week”, (4) “several times a week”. This is one of the most validated measures on bullying victimization [45] with sound construct validity [44].

*School connectedness.* The Psychological Sense of School Membership Scale (PSSM) [46] assesses students’ connectedness with their school. It has 18 items, and a Dutch translation is available. A shortened, 2-item version has been administered in one Dutch study, showing a satisfactory internal consistency of .76 [47]. This short version contains the items: “I feel like a real part of my school” and “I feel proud of belonging to my school”. In this study, this short version will be used.

#### Statistical analyses

All statistical analyses will be conducted in R [48] by an independent researcher. Reporting of the results will be conducted in accordance with the (extended) CONSORT statement [23]. Analyses will be conducted based on the intention-to-treat (ITT) principle. The primary ITT analyses will be performed using linear mixed models, which adequately deal with missing at random data and can be used to account for the nested structure of the data; students nested within classes and repeated assessments nested within students [49]. Time, condition, and time by condition interactions will be specified as fixed effects to examine the effectiveness of the intervention on continuous primary and secondary outcomes. Baseline scores of the corresponding outcome will simultaneously be entered as fixed factors in the model to account for baseline imbalances. In accordance with the CONSORT statement [23], it will not be explicitly tested whether conditions statistically differ in their baseline characteristics. Hence, the decision whether models will be adjusted for additional covariates will not be based on whether statistical differences in these covariates exist at baseline. Instead, models will primarily be reported that are not adjusted for additional covariates. In an additional sensitivity analysis, it will be examined whether adjusting these models for the following baseline variables substantially changes conclusions drawn from the analyses: gender, age, immigration background, depressive symptoms, well-being, and life satisfaction. Post-hoc tests will be conducted to examine between-group differences at each timepoint using analyses of covariance (ANCOVA), including baseline scores as covariate. Based on estimated marginal means and corresponding standard errors from linear mixed models, between-group effect sizes at each timepoint will additionally be expressed as Cohen’s *d* with 95% confidence intervals.

Mediation analyses will be performed to examine potential working mechanisms of the effect of the intervention. Research has shown that there is an association between school climate and mental health of students [50]. Positive relationships between students and their teachers or peers increased psychosocial well-being [50]. Moreover, teacher support reduced depressive symptoms [51]. In addition, higher school connectedness (attachment and belonging to school) was positively associated with students’ psychosocial well-being [50] and acted as a buffer against depressive symptoms and anxiety [51, 52]. Finally, causal associations were found between bullying and depression [53]. Therefore, the following variables will be tested as potential mediators: classmate support, teacher support, school connectedness, and bullying. The categorical variable condition will be included as independent variable in all mediation models (0 = control, 1 = intervention), and the observed scores of primary or secondary outcomes at follow-up as dependent variable. Total, direct, and (total) indirect effects with 95% bootstrapped confidence intervals will be calculated for all mediation models [54, 55].

Furthermore, exploratory moderator analyses will be conducted to examine whether the effect of the intervention on primary and secondary outcomes depends on a priori defined variables. Various sociodemographic factors have an influence on interventions focused on depressive symptoms or well-being. Research has shown that girls might experience more benefits from depression prevention programs than boys [56]. Moreover, older participants might benefit more from cognitive-behavioral therapy [24, 57]. In addition, research has shown that depression prevention programs are likely to be more effective for adolescents with ethnic minority backgrounds [24], since they report more problems with mental health compared to adolescents with ethnic majority backgrounds [32]. Therefore, the following variables will be examined as potential moderators: level of baseline CES-D depressive symptoms, gender, age, and immigration background. Separate linear mixed models with condition, the putative moderator, and the interaction of these two as fixed effects will be used to examine potential moderation effects.

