### Design of the RCT

The effectiveness of HL will be tested within a cluster RCT with two conditions: an intervention condition (receiving HL during the study) and a control condition (care as usual, HL will be delivered after the final follow-up assessment). Participating classes will be randomly assigned to either the intervention or the control condition and will be equally distributed across the two conditions within each schoolyear. This design is chosen to avoid a skewed distribution of participants over the two conditions due to school effects. The randomization will be conducted by an independent statistician. Three assessments will be performed in the study: T0 (pre-test, before the start of HL in intervention group); T1 (3-months follow up); T2 (6-months follow-up).

Data will be collected in two cohorts: the first cohort is planned in the 2021-2022 school year and the second cohort is planned in 2022-2023 school year.

See Fig. 2 for the flowchart of the study and Table 1 for an overview of the schedule of enrolment, interventions, and assessment.

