#### Study population

##### Eligibility criteria and recruitment of schools

To provide HL at a school, three different parties need to be involved: schools, mental health organizations that provide the professionals that deliver HL, and – in most cases – the municipality that pays for HL. Schools, mental health organizations, and municipalities were recruited via the website and newsletter of the Trimbos Institute and the HL website. Schools are included in the study if they offer pre-vocational education in at least two first-year or two second-year classes (age 12-14 years). This may also include “combination classes” that contain students from both pre-vocational and higher educational levels.

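### Classes appear to be balanced between arms within school, but no planned model contains school, so standard errors may be somewhat too large and the test conservative

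*Protocol article*

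**What the plan says.** Under Design of the RCT, classes are the unit of randomisation and "will be equally distributed across the two conditions within each schoolyear". The reason follows: "This design is chosen to avoid a skewed distribution of participants over the two conditions due to school effects". Sample size plans on both arms being present in each school: "Assuming an average of 4 classes of 22 students per school (divided across intervention and control condition", and "this will require 48 classes from about 12 schools". A school is eligible only if it has "at least two first-year or two second-year classes (age 12-14 years", which is what a split within school needs.

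Under Statistical analyses, the clustering levels are "students nested within classes and repeated assessments nested within students". On the fixed part, "Time, condition, and time by condition interactions will be specified as fixed effects", together with the baseline value of the outcome. The main models carry no further covariates. The sensitivity analysis adds age, gender, immigration background and the baseline scores for depression, well-being and life satisfaction. School appears in neither model. Nor do grade or cohort, although "Data will be collected in two cohorts".

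**The concern.** An analysis should normally reflect the restrictions placed on the randomisation. If each school contributes equally to both arms, differences between schools cancel from the comparison of arms. A model that knows only classes cannot see this. It places the between-school variance in the class random effect and charges it to the standard error of the condition effect. The trial would then report less precision than its design delivers, in a setting where the target effect is small (d = 0.20) and a few points of power matter. The error is on the safe side: it does not bias the estimate or inflate the type I error.

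**Working it through.** **Inputs from Sample size.** d = 0.20, two-sided 5%, 80% power; 22 students per class; ICC 0.02; cluster-size variation (CV) 0.17; baseline correlation r = 0.30; 40% without consent; 48 classes in about 12 schools. The cited ICC sources give 0.008, and 0.01 to 0.07 across countries. **Assumption:** the share s of the ICC that lies between schools is not given, so it is varied from 0 to 1.

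**The plan's own figure.** Design effect DE = 1 + ((1 + CV²)m − 1)·ICC. With m = 22 this is 1.4327. Without clustering 392.4 per arm are needed. 392.4 × 1.4327 × 0.56 = 314.9, which is the stated 315. The factor 0.56 = (1 + r)/2 − r² is that for the average of two follow-ups adjusted for baseline. 315/0.60 = 525, as stated.

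**Setting for the check.** Analysed per class: 22 × 0.60 = 13.2. Per arm: 24 classes, so 24 × 13.2 = 316.8 students. The primary endpoint is 6 months alone, so the variance factor is 1 − r² = 0.91. This factor affects the power figures but cancels from the ratio of standard errors.

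**Formulas.** With an exactly equal split in each school:

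- Reported SE without school: √(2 × 0.91 × DE(ICC)/316.8)
- True SE, also the reported SE with school in the model: √(2 × 0.91 × DE(ICC(1 − s))/316.8)
- R = reported SE / true SE
- Actual alpha without school: 2Φ(−1.96R)
- Power without school: Φ(0.20/true SE − 1.96R)
- Power with school: Φ(0.20/true SE − 1.96)

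**Worked case, ICC 0.02, s = 0.5.** DE(0.02) = 1.2516 gives a reported SE of 0.0848. DE(0.01) = 1.1258 gives a true SE of 0.0804. R = 1.054, so alpha = 2Φ(−2.067) = 0.039. Power without school is Φ(2.487 − 2.067) = 66%; with school it is Φ(2.487 − 1.960) = 70%.

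| ICC | School share | SE excess | Actual alpha | Power without / with school (normal) |
|---|---|---|---|---|
| 0.008 | 0.5 | 2.4% | 4.5% | 72% / 73% |
| 0.008 | 1 | 4.9% | 4.0% | 72% / 75% |
| 0.02 | 0.5 | 5.4% | 3.9% | 66% / 70% |
| 0.02 | 1 | 11.9% | 2.8% | 67% / 75% |
| 0.07 | 0.5 | 14.3% | 2.5% | 48% / 59% |
| 0.07 | 1 | 37.1% | 0.7% | 48% / 75% |

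At share 0 the excess is nil and alpha is 5% at every ICC.

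**Small-sample degrees of freedom.** Without school: 48 − 2 = 46. School takes 11, leaving 35; if grade and cohort could both be estimated as well, 33 would remain. Noncentral t with df 46 against the least favourable df 33, at ICC 0.02:

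| School share | Power without school | Power with school |
|---|---|---|
| 0 | 63.7% | 62.9% |
| 0.25 | 64.0% | 65.1% |
| 0.5 | 64.3% | 67.5% |

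At ICC 0.008 and half share the figures are 69.6% and 70.5%.

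**Simulation.** 20,000 trials with 12 schools of 4 classes (2 per arm), 13 students per class, ICC 0.02, half share, no baseline adjustment. The empirical SE was 0.084 with or without the school term. The class-only model reported 0.088 on average, with type I error 3.9% and power 59%. With school as a fixed effect, the reported SE was 0.084, type I error 5.0% and power 63%.

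**The case against.** Four points on the other side carry weight.

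- **The estimate loses nothing.** A reader might infer that the model throws the balance away. It does not: the simulation gives the same empirical SE with and without school. Only the reported SE, interval and test fail to take credit.
- **The excess is conditional.** A reader might infer that standard errors are certainly too large. That needs between-school variance, whose size the protocol does not state. At zero share nothing is gained and under one point of power is lost. The baseline score already in the model may also absorb part of any school variance. The large figures need an ICC of 0.07, the top of the cited range, or a high school share.
- **Balance within school is inferred.** The literal wording is balance within each schoolyear, which could mean grade or calendar year. The stated reason and the split of each school's classes make within-school balance the natural reading, but no stratification rule is written down. A reader might take grade and cohort as established strata too; one ambiguous word cannot show that. Cohort is aliased with school if each school joins only one cohort, and grade may be largely so, since a school can qualify with classes of a single year.
- **Detail may sit in an analysis plan.** This stands only in part. The article itself sets out the nesting levels, the fixed effects and the sensitivity covariates, and school is in none of them.

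The power figures below 80% above come from using a single follow-up. They raise a separate sample-size question and add no weight to this point.

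**Conclusion.** The point holds as a conservative inefficiency, not as a threat to validity. The design appears to balance on school and the stated models leave school out. With 13.2 students analysed per class, the reported standard error exceeds the true one by 0 to 5% at ICC 0.008, 0 to 12% at 0.02 and 0 to 37% at 0.07, as the school share runs from 0 to 1. At the planning ICC, the gain from including school runs from a loss of under one power point at zero share to about 3 points at half share, after small-sample degrees of freedom. This rests on an even split of classes within each school, on the assumed school share, and on an ICC that baseline adjustment leaves unchanged. The ranges are therefore towards the upper end. Claims of bias, of inflated type I error or of a certain loss of precision are not supported by the protocol.

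**What to change.** State the balancing factor unambiguously: school, or grade within school. Include that factor as a fixed effect in the primary and secondary mixed models, keep class as the random cluster effect, and use small-sample degrees of freedom. Add cohort or grade only where it is not already absorbed by the school term.

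The change is one of analysis wording and is best made before outcome data are seen. It uses about a dozen of the 46 class-level degrees of freedom: the critical t value rises from about 2.01 to about 2.03, and power falls by less than one point if schools turn out not to differ.
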